### Sample size calculation

No prospective studies have performed CCT (including both CACS and CCTA) in women with reproductive disorders as part of long-term cardiovascular follow up. The estimation of the expected necessary sample size is based on α = 0.05 and desired power = 0.90. In addition, the background prevalence of coronary plaque (both non-calcified and calcified) in asymptomatic, healthy females ≥ 45 years old based on the CCTA study by Kim et al. (2013) is estimated 6.7% [83]. We presume a relative risk of around 2 for the development of CVD is women with reproductive disorders [44]. This leads to an (conservative) estimated prevalence of coronary artery disease (plaque) of 13.4% (95% CI 10.0 - 17.6) and a minimal sample size of at least 261 CCT’s in both the HPD and the PCOS/POI group.

Based on these results and given the radiation-induced health risks, initial inclusion will be confined to women who are 45-55 years old and we will perform an interim analysis after 300 CCT’s (100 in patients with HPD, 100 in patients with PCOS and 100 in patients with POI). If the prevalence of plaque as seen on CCTA is ≥ 10%, which is the lower bound of the 95% CI in our estimated prevalence of coronary artery disease, we expect to find significant differences compared to controls. In that case, we will perform the remaining 300 CCT’s (200 in patients with HPD and 100 in patients with PCOS/POI), leading to a total of 300 CCT’s in patients with HPD and 300 CCT’s in patients with PCOS/POI. The age range (40-45 years and/or ≥ 55 years) and group composition for later inclusion may be adapted based on the findings of the interim analysis. If the prevalence of plaque as seen on CCT is ≤ 10%, we do not expect to find any significant differences compared to controls and therefore we will withdraw the remaining CCTA’s and focus on CACS only.

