### Imaging

CACS acquired with CCT has been shown to have superior predictive value for CVD events to traditional risk factors, risk factor scores and serum biomarkers in asymptomatic persons [50]. Contrast-enhanced CCTA may have additional value over CACS as it can also identify non-calcified plaques, and thereby the total atherosclerotic burden, and assess the presence of coronary luminal narrowing [51–54]. As calcification of plaque occurs at a relatively late stage in atherosclerosis, significant coronary atherosclerosis may be visualized earlier by visualizing the non-calcified coronary plaque with CCTA. Data of CCT as a diagnostic tool, i.e. CACS or CCTA, is scarce and inconclusive for women with reproductive disorders.

Several studies have assessed the presence of coronary calcium in PCOS. Although some of these studies showed an increased CACS in women with PCOS, a recent large, cross-sectional study could not find an association with PCOS and CACS [55–58].

In a retrospective cohort study published in 2007, the relation between HPD and coronary calcification later in life was assessed in 491 women (mean age 66.8 years, standard deviation 5.4 years) [59]. Coronary calcifications (Agatston score ≥ 1) were found in 305 women (62.9%).This study showed that a self-reported history of hypertension during pregnancy is related to higher CACS in the 7th decade of life (Odds ratio (OR) 1.57, 95% CI 1.04 - 2.37). In an adjusted model correcting for age, BMI, waist:hip ratio, systolic blood pressure and diastolic blood pressure the relation did not reach statistical significance anymore (OR 1.52, 95% CI 0.96 - 2.39) [59]. Other retrospective studies assessing coronary artery disease (CAD) by catheter coronary angiography in women suspected for CAD and with a history of HPD showed contrasting results [60, 61]. A recent prospective cohort study conducted among 40 former pre-eclamptic women and 40 age- and parity-matched healthy controls showed increased CACS in former pre-eclamptic women at a mean age of 59.5 ± 4.6 years. The unadjusted OR for having higher CACS due to preeclampsia was 3.54 (95% CI 1.39 - 9.02), although the adjusted model correcting for BMI and hypertension did not reach statistical significance anymore [62].

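### The 6.7% background plaque rate comes from women aged 45 and over with no stated ceiling, so the 13.4%, the 10% interim cut-off and the 261 are not matched to a cohort confined to 45-55

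*Protocol article*

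**What the plan says.** All the planning figures are in the protocol article, Sample size calculation.

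- **Background rate.** The starting point is the "background prevalence of coronary plaque (both non-calcified and calcified) in asymptomatic, healthy females ≥ 45 years old", which "is estimated 6.7"%. No ceiling on age is stated.
- **Effect.** "We presume a relative risk of around 2 for the development of CVD" is the stated assumption, and it is applied to plaque prevalence.
- **Expected prevalence.** The product is an "estimated prevalence of coronary artery disease (plaque) of 13.4% (95% CI 10.0 - 17.6"), which the section describes as conservative.
- **Sample size.** With "α = 0.05 and desired power = 0.90", the section arrives at "a minimal sample size of at least 261 CCT’s in both the HPD and the PCOS/POI group".
- **Ages enrolled.** In the same section, "initial inclusion will be confined to women who are 45-55 years old". Participant characteristics gives the same range.
- **Interim rule.** After 300 scans (100 each in HPD, PCOS and POI), plaque prevalence is compared with 10%, identified as the lower limit of the interval around 13.4%. At or above 10% the remaining 300 scans go ahead. At or below 10% the remaining CCTAs are withdrawn and only calcium scoring continues.
- **Later change.** The age range for subsequent inclusion may be altered after the interim look, to 40-45 and/or 55 and over.

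**The concern.** The cut-off is an absolute prevalence, but the question it is meant to answer is relative: do these women have more plaque than comparable women without a reproductive disorder? An absolute threshold answers that only if the background rate behind it applies to women like those scanned. Here the background covers everyone from 45 upward, while the scanned women stop at 55.

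Plaque accumulates with age, so an average over an open-ended range probably exceeds the rate at 45-55. In that case, prevalence among the first 300 could fall to 10% or below because the women are younger than the reference group, even though the assumed doubling is true. The plan would then conclude that no difference from controls is to be expected.

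The loss would be the remaining CCTAs. CCTA is the only modality in the study that shows non-calcified plaque, and the Imaging section of the Background says this may reveal atherosclerosis earlier than calcium does.

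**Working it through.** **Inputs from the document:** background 6.7%, relative risk 2, interval 10.0-17.6%, α 0.05, power 0.90, 300 women at the interim look, cut-off 10%.

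**Assumed inputs:** the background at ages 45-55, which the document does not give, varied from 4% to 8%; and pooling of the three disorder groups at the interim look.

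**Step 1. Reproduce the plan's figures.**

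- Expected prevalence: 2 × 6.7% = 13.4%. This agrees.
- Interval: the Wilson formula is [p + z²/2n ± z√(p(1−p)/n + z²/4n²)] / (1 + z²/n). With p = 0.134, n = 300 and z = 1.96 it gives 0.1386 ± 0.0386, or 10.0% to 17.7%. The plan has 10.0-17.6, so a Wilson interval at n = 300 is the apparent source.
- Sample size: the 261 does not follow from the stated inputs. A two-sided comparison of 13.4% with 6.7% at 90% power needs 422 per group with equal groups. A figure of 261 appears only with an unstated ratio, for instance about 3.4 controls per patient. That is a separate matter. What counts here is that the 261 starts from the same 6.7%.

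**Step 2. What the fixed 10% asks of the relative risk.** The ratio is 10% divided by the background: 10/6.7 = 1.49, 10/6 = 1.67, 10/5 = 2.0, 10/4 = 2.5. Once the background is 5%, a true doubling lies exactly on the cut-off.

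**Step 3. Chance of withdrawal when the relative risk is exactly 2.** X is binomial with n = 300 and p = 2 × background. The text withdraws CCTA at 10% or below, so the main figure is P(X ≤ 30). Exactly 10% also meets the rule for continuing, so P(X < 30) is shown as well. The last column rebuilds the cut-off as in Step 1, as the Wilson lower limit at n = 300.

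| Background at 45-55 (assumed) | Prevalence at RR 2 | P(X ≤ 30) | P(X < 30) | Rebuilt cut-off |
|---|---|---|---|---|
| 8.0% | 16.0% | 0.2% | 0.1% | 12.3% |
| 6.7% (as planned) | 13.4% | 4.6% | 3.1% | 10.0% |
| 6.0% | 12.0% | 16% | 12% | 8.8% |
| 5.0% | 10.0% | 55% | 47% | 7.1% |
| 4.0% | 8.0% | 91% | 88% | 5.4% |

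A fall of 1.7 percentage points in the background, from 6.7% to 5.0%, moves the chance of withdrawing CCTA from about 1 in 20 to slightly more than 1 in 2. The choice of boundary does not change that picture.

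**The case against.** The strongest reply is that the direction of the error is not established. A reader might infer that 13.4% and 10% simply are too high. To show that, one would need the age mix of the reference study or its rate at 45-55, and the document gives neither. If most reference women were close to 45-55, the age effect would be small.

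The reference women were also asymptomatic and healthy, whereas this cohort comes from cardiovascular screening and excludes only serious illness, renal dysfunction and previous infarction. That difference pushes the true background upward. This objection stands, and it limits the claim about direction to the age effect taken alone.

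A reader might also cite the Imaging section, where "Coronary calcifications (Agatston score ≥ 1) were found in 305 women (62.9"%) at mean age 66.8, as proof of the age gradient. It is one age point, in another cohort, for calcium rather than plaque. Used quantitatively it does not help. The odds are 0.629/0.371 = 1.70. If they double every 7 or 10 years (an assumption), moving 16.8 years down to age 50 divides them by 2^2.4 or 2^1.68. The result is 0.32 or 0.53, a prevalence of about 24% or 35%, far above 6.7%. The figure is therefore not comparable with the reference rate and cannot show that 6.7% is too high.

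A further inference would be that a final test against 6.7% loses power or understates the relative risk. The plan speaks of differences from controls and of chi-square comparisons between groups. It does not state a test against a fixed 6.7%, so that inference has no footing.

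Lastly, calcium scoring continues whatever the interim look shows, and CACS of 100 or more is one arm of the primary outcome. The age range may also be changed afterwards. The first point limits the damage. The second does not repair the rule, because the decision is taken on the women aged 45-55.

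**Conclusion.** The concern holds as a mismatch. A rate for healthy women of 45 and over with no stated upper limit is carried, without adjustment, into the expected prevalence, the interim cut-off and the sample size of a cohort confined to 45-55. The age difference alone probably makes the 13.4% and the 10% too high. The net error after allowing for healthy selection cannot be determined from the document.

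What can be shown is how much depends on the answer. If the relative risk is truly 2, the chance of withdrawing CCTA is about 5% at the planned background, 16% at 6%, 55% at 5% and 91% at 4%. It would be well under 1% if the background were 8%. These figures assume a pooled count in 300 women, a relative risk of exactly 2 and withdrawal at 30 or fewer. The backgrounds other than 6.7% are assumptions. A rule that can remove a main imaging modality should not rest on an unmatched rate when the consequence is this sensitive to it.

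**What to change.** Before the interim look:

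1. Replace the 6.7% with the reference study's rate for women aged 45-55, or with its age-specific rates standardised to the ages actually enrolled.
2. Recompute from it the expected prevalence, its interval, the interim cut-off and the 261. By the plan's apparent Wilson logic at n = 300, the cut-off would be about 8.8% for an expected 12% and 7.1% for an expected 10%.
3. State the rule's chance of withdrawing CCTA when the relative risk is 2.
4. If no rate for these ages can be obtained, show the cut-off and that chance over backgrounds on both sides of 6.7%, and do not let 10% alone trigger the withdrawal of CCTA.

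The cost is a recalculation, a short amendment to the sample size section, and possibly a less favourable expected prevalence with a larger required sample.

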### Statistical analysis

Data analysis will be performed using SPSS. A probability (p) less than 0.05 will be considered significant. The characteristics of participants will be described using means +/− standard deviations for continuous variables using a two tailed independent t-test for comparison between groups (e.g. plaque burden). Categorical variables will be expressed as numbers (percentages) or medians (with inter quartile ranges) and compared with a chi-square test (e.g. CACS percentiles). Identical tests will be performed for circulating biomarkers. If several variables are identified to be statistically associated with cardiovascular risk factors, multiple linear regression or multiple logistic regression will be performed to identify the most important associations, appropriate to the endpoint chosen.

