There is mounting evidence that intracranial carotid artery calcifications are associated with increased large artery and intracranial artery stiffness, as well as ischemic stroke, white matter abnormalities and cognitive impairment [63, 64]. Recent studies found a relationship between carotid siphon calcium (CSC) and white matter hyperintensities and lacunar infarcts [65–67]. Other studies, however, could not confirm these findings [68–70].

Collectively, previous studies indicate an association between women with reproductive disorders and CVD later in life. Current risk profiles are inadequate to establish future CVD risk in still relative young premenopausal women. The aim of this study is to assess the diagnostic value of cell-based biomarkers, CCT imaging (both non-contrast CACS and contrast enhanced CCTA) and non-contrast CSC in patients with a reproductive disorder to detect CVD.

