## Methods

### Study design and study setting

In this multicenter, prospective, cross-sectional study of patients with a reproductive disorder (PCOS, POI or HPD) we aim to assess the diagnostic value of cell-based biomarkers and CT imaging of the coronary arteries and carotid siphon in the detection of CVD. Patients will be invited to participate at their regular cardiovascular screening, which is performed at two large University Medical Centers in Utrecht (UMC Utrecht) and Rotterdam (Erasmus MC) in the Netherlands.

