### Single center side study: Serum biomarkers and non-invasive vascular measurements

Classical cardiovascular biochemical risk factor assessment (glucose, insulin, triglycerides, total cholesterol, low-density lipoprotein cholesterol and c-reactive protein) and a general hematological profile (total red and white blood cells and differential counts of nucleated cells) will both be determined.

As part of a single center side study in the UMC Utrecht, the neutrophil, monocyte, and lymphocyte cell numbers and subtype distribution will be examined based on established cell surface marker expression by flow cytometry analysis [78, 79]. Peripheral blood mononuclear cells and circulating endothelial cells will be isolated and sorted directly after drawing blood. To assess histone modification in inflammatory genes, monocytes are cultured in the presence of atherosclerosis associated antigens (oxLDL, HSP). Plasma will be used to isolate and detect (endothelial) microparticles. Proteomics on isolated microparticles will be performed on selected samples and analyzed. Lupus anticoagulants are phospholipid-dependent coagulation inhibitors that are detected with a functional assay based on a clotting test. Platelet reactivity can be assessed with the platelet activation test (PACT), a whole blood functional test of the total platelet response capacity.

Arterial stiffness measured by pulse wave velocity (PWV) is a predictor of cardiovascular events. The Arteriograph (TensioMed, Budapest, Hungar. EC Directive 93/42/EEC, ISO 13485:2003, ISO 13485:2004) is an oscillometric arterial stiffness measurement, which will be performed directly before the CCT in the UMC Utrecht.

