### Outcome

The primary outcome is the presence of relevant CAD that will be defined as one or more of the following on CT: a CACS ≥100 AU or luminal stenosis ≥ 50%. All measurements will be discussed with participants individually under supervision of a vascular specialist. For management of cardiovascular risk factors, the current guideline on European Guidelines on cardiovascular disease prevention will be used [80]. All patients with relevant CAD are discussed with a cardiologist. Management and treatment decisions are left to the discretion of the cardiologist. As a general rule, participants with a CACS of 100-400 AU without obstructive CAD will receive lifestyle advice and may be recommended to initiate treatment with statins [81, 82]. Participants with a CACS ≥ 400 AU or coronary artery stenosis ≥ 50% will be offered a consultation with a cardiologist to discuss management options. Other relevant cardiac findings will be discussed with the cardiologist. If incidental extra-cardiac findings, such as lung or liver lesions, are considered to be of clinical importance, recommendations of further testing, follow-up or referral to another specialist will be made.

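### The biomarker aim is diagnostic value, but the stated analysis (group tests, then a conditional association regression with no fixed endpoint) yields none

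*Protocol article*

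**What the plan says.** The aim appears twice in the protocol article. The Background, at the end of its Imaging subsection, says: "The aim of this study is to assess the diagnostic value of cell-based biomarkers, CCT imaging". Study design and study setting repeats it and names the target: "we aim to assess the diagnostic value of cell-based biomarkers and CT imaging of the coronary arteries and carotid siphon in the detection of CVD".

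The Outcome section defines a CT endpoint, relevant CAD, as a CACS of at least 100 AU or a luminal stenosis of at least 50%. It introduces it thus: "The primary outcome is the presence of relevant CAD that will be defined as one or more of the following on CT". It does not tie the biomarkers to that endpoint.

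Statistical analysis sets out three steps that bear on the biomarkers:
- Continuous variables are compared "using a two tailed independent t-test for comparison between groups (e.g. plaque burden", and categorical variables by chi-square. The section does not say which groups are compared.
- For the biomarkers: "Identical tests will be performed for circulating biomarkers".
- Multiple linear or logistic regression may follow, under this condition: "If several variables are identified to be statistically associated with cardiovascular risk factors". Its purpose is to find the strongest associations, and its endpoint is left to be chosen.

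The cell-based biomarkers are measured in one of the two centers, under a heading that calls this a single center side study. The Discussion describes the biomarker work as a substudy of how the biomarkers are associated with coronary CT.

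**The concern.** Diagnostic value is a statement about classification: how well a marker separates women who have the condition from women who do not, and whether it adds to what is already known about them. A test of a difference in means or proportions answers another question. With enough women, a difference too small to be useful for detection reaches p < 0.05.

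This aim could be addressed. The study produces a CT classification against which the blood markers can be judged, and it measures the classical risk factors over which a marker would have to add something. The stated analysis uses neither for this purpose. Followed as written, it could report a marker as significant and leave readers to take that as diagnostic value. The stated aim would then be unanswered or over-claimed. The primary CT outcome is not affected.

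**Working it through.** The plan gives no accuracy figure for any biomarker, so there is nothing to reproduce. The check compares aim with method, then illustrates the size of the gap.

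**Aim against method**

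1. *Group tests, if the groups are the diagnosis groups (HPD versus PCOS/POI).* The section's own examples, plaque burden and CACS percentiles, are CT findings compared between groups. This suggests that the groups are the reproductive diagnoses, though the text does not say so. Such a test does not compare women with and without CAD, so it says nothing about detecting CAD.
2. *Group tests, if the groups are CAD yes and CAD no.* The result is a p-value for a mean difference. It is not a measure of discrimination, and it does not show value beyond the classical risk factors.
3. *Regression.* It runs only if variables prove to be associated with cardiovascular risk factors. That trigger is not CAD on CT. A logistic model for relevant CAD could yield an AUC, but the text does not commit to that endpoint or that use.
4. *Discussion.* It describes association, which group tests and regression can serve. That is a different aim from the one stated twice earlier.

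**How little a significant test implies**

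Inputs:
- Two-sided α = 0.05 (Statistical analysis).
- Prevalence of any plaque 13.4% (Sample size calculation). This is the plan's assumed plaque prevalence, not the prevalence of relevant CAD.
- Number of women with biomarkers: not given. Assumed 300. The whole planned cohort of 600 serves as an upper bound, since the side study runs in one center.
- Marker normally distributed with equal variance in both groups.

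Formulas: smallest significant standardized difference d = 1.96 × √(1/n₁ + 1/n₀); AUC = Φ(d/√2); sensitivity at 90% specificity = 1 − Φ(1.2816 − d).

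- 300 women: 0.134 × 300 ≈ 40 cases and 260 non-cases. d = 1.96 × √(1/40 + 1/260) = 1.96 × 0.1698 = 0.333. AUC = Φ(0.235) = 0.593. Sensitivity = 1 − Φ(0.949) = 17%.
- 600 women: 0.134 × 600 ≈ 80 cases and 520 non-cases. d = 1.96 × √(1/80 + 1/520) = 1.96 × 0.1201 = 0.235. AUC = Φ(0.166) = 0.566. Sensitivity = 1 − Φ(1.046) = 15%.

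An AUC of 0.50 is no discrimination. A marker at this threshold is significant and close to useless for detection.

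**Precision if accuracy were estimated**

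Hanley-McNeil standard error with an assumed AUC A = 0.70, Q₁ = A/(2 − A) = 0.538 and Q₂ = 2A²/(1 + A) = 0.576:

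SE² = [A(1 − A) + (n₁ − 1)(Q₁ − A²) + (n₀ − 1)(Q₂ − A²)] / (n₁n₀)

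- 40 and 260: SE² = (0.21 + 39 × 0.0485 + 259 × 0.0865)/10,400 = 0.00236; half-width 1.96 × 0.0485 = 0.095.
- 20 and 280 (6.7% of 300, the plan's background plaque prevalence): half-width 0.13.
- 80 and 520: half-width 0.07.

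**The case against.** The strongest reply is that the document already treats the biomarkers modestly. The abstract presents the study as a CT study with biomarkers in addition, the section heading discloses a single-center side study, and the Discussion speaks of association. On that reading, group tests and regression suit the question, and the two aim statements are loosely worded. A condensed article may also leave accuracy measures to a full protocol or analysis plan that is not shown.

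Part of this stands. The absence of an ROC section is not a finding in itself. What remains is visible in the text: an aim stated twice, and a stated method that does not answer it. The Discussion's wording confirms the inconsistency without resolving it.

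A reader might infer three stronger points that the document does not support:
- *That the group tests are the sole biomarker analysis.* The regression sentence follows directly and does not exclude biomarkers, and the Discussion announces a biomarker–CT substudy. These fail to close the gap, but they exist.
- *That the proteomics will overstate accuracy.* The text says "Proteomics on isolated microparticles will be performed on selected samples and analyzed" and gives no selection rule. Selection by CT result would be a supposition.
- *That relevant CAD will be too rare for any accuracy analysis.* The document gives no expected prevalence for relevant CAD, so no case count can be derived from it.

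It is also fair to say that the AUC illustration reflects a general property of significance tests. It shows the size of the gap at plausible numbers and does not recompute a figure in the plan.

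**Conclusion.** The mismatch between aim and analysis holds. None of the three descriptions of the biomarker work (group tests with undefined groups, conditional regression without a fixed endpoint, association substudy) yields diagnostic value. At the assumed 300 women and 13.4% prevalence, passing the planned test requires an AUC of only about 0.59; at the upper bound of 600 women, about 0.57. These figures rest on an assumed side-study size, on the plan's prevalence of any plaque and on normal, equal-variance markers. The mismatch itself rests on the text alone. It should be corrected, but it concerns a disclosed side study and leaves the primary outcome untouched.

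**What to change.** - **Statistical analysis:** replace the sentence that assigns identical tests to the biomarkers. For each marker, report the AUC with 95% CI against relevant CAD as defined under Outcome. Add any plaque as a supportive reference, limited to women who had CCTA, because the interim rule in Sample size calculation may withdraw CCTA for later participants. Report also the change in AUC when the marker is added to age and the classical risk factors. If group comparisons are kept, name the groups.
- **Background (end of Imaging) and Study design and study setting:** restate the biomarker aim as exploratory and single-center, consistent with the side-study section and the Discussion.

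This changes wording and analysis and needs no additional scan; the classical risk factors are already among the planned measurements. The price is statistical: at an AUC of 0.70 the half-width is about 0.10 with 40 cases and wider with fewer, so the claim about the biomarkers becomes more modest.

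### Groups are compared without adjustment and regression depends on a significance screen, so an interim change in age range could confound any HPD versus PCOS/POI comparison

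*Protocol article*

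**What the plan says.** The Statistical analysis section names two between-group tests and gives an imaging outcome as the example for each. Continuous variables are compared "using a two tailed independent t-test for comparison between groups (e.g. plaque burden", and categorical variables are "compared with a chi-square test (e.g. CACS percentiles". The same tests are applied to the circulating biomarkers. No covariate or stratum is named.

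Regression is conditional: "If several variables are identified to be statistically associated with cardiovascular risk factors, multiple linear regression or multiple logistic regression will be performed". Its purpose is "to identify the most important associations, appropriate to the endpoint chosen". Adjusting the group comparison is not mentioned.

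The Sample size calculation section describes two recruitment stages. The first, in women aged 45-55, has "100 in patients with HPD, 100 in patients with PCOS and 100 in patients with POI". If interim plaque prevalence is at least 10%, the second has "200 in patients with HPD and 100 in patients with PCOS/POI". The same section adds: "The age range (40-45 years and/or ≥ 55 years) and group composition for later inclusion may be adapted" in the light of the interim findings.

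The primary outcome (Outcome section) is relevant CAD, meaning CACS of at least 100 AU or stenosis of at least 50%. Under Study design and study setting, the authors state "we aim to assess the diagnostic value of cell-based biomarkers and CT imaging".

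**The concern.** Three stated features interact. Diagnosis is unevenly spread over the two stages, the stages may differ in age range, and the planned tests adjust for neither age nor stage. Coronary calcium and plaque depend on age, so a second stage recruited at other ages could create or hide a difference between HPD and PCOS/POI that has nothing to do with diagnosis.

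The conditional regression does not protect against this. It is triggered by association with cardiovascular risk factors, not with relevant CAD, and may not be run at all. If it is run, nothing ensures that age enters the model. A confounder should be adjusted for because of its role in the design, whatever its p-value.

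The protocol's own background shows why adjustment matters. It says that the extent to which POI, like PCOS, is independently associated with CVD is unclear. It also cites two HPD calcium studies in which the association lost statistical significance after adjustment.

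**Working it through.** The plan gives no figure of its own for this point, so the check is how far a stage difference carries into the crude contrast.

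**Inputs from the Sample size calculation section (branch with interim prevalence of at least 10%)**
- Stage 1: HPD 100, PCOS/POI 100 + 100 = 200.
- Stage 2: HPD 200, PCOS/POI 100.
- Share recruited in stage 2: HPD 200/300 = 66.7%; PCOS/POI 100/300 = 33.3%.

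**Assumptions**
- No effect of diagnosis: within a stage, both groups have the same prevalence.
- Prevalence is p in stage 1 and m × p in stage 2. The article gives no prevalence by age, so m is varied from 0.5 to 2.

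**Crude contrast**
- HPD: p(100 + 200m)/300 = p(1 + 2m)/3.
- PCOS/POI: p(200 + 100m)/300 = p(2 + m)/3.
- Difference: p(m − 1)/3, one third of the between-stage difference.
- Ratio: (1 + 2m)/(2 + m).

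Ratios: m = 0.5 gives 2/2.5 = 0.80; m = 1 gives 1; m = 1.5 gives 4/3.5 = 1.14; m = 2 gives 5/4 = 1.25.

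**Age.** The same weights apply to mean age. Assume a stage-1 mean of 50.
- Stage-2 mean 42.5 (only 40-45 years added): HPD (100 × 50 + 200 × 42.5)/300 = 45.0; PCOS/POI (200 × 50 + 100 × 42.5)/300 = 47.5.
- Stage-2 mean 60: HPD 56.7; PCOS/POI 53.3.

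**False-positive rate of the unadjusted two-sided 5% chi-square.** Let Δ be the absolute crude difference, SE0 = √(2p̄(1 − p̄)/300) the standard error the test uses, and SE1 the true standard error from the within-stage binomial variances. The rejection rate is about Φ((Δ − 1.96 × SE0)/SE1).

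Example with p = 13.4% (the article's expected prevalence) and m = 2: the group prevalences are 22.33% and 17.87%, so Δ = 0.0447 and p̄ = 0.201. SE0 = 0.0327 and SE1 = 0.0323, giving about 27%.

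| Stage-2/stage-1 ratio m | Crude ratio | False-positive rate, p = 13.4% | False-positive rate, p = 6.7% |
|---|---|---|---|
| 0.5 | 0.80 | 15% | 10% |
| 1 | 1.00 | 5% | 5% |
| 1.5 | 1.14 | 11% | 8% |
| 2 | 1.25 | 27% | 15% |

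Simulation with 200,000 replicates agrees. A stage-stratified Cochran-Mantel-Haenszel test stays at 4.9-5.0% throughout.

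**Price of stratifying by stage.** Information is proportional to n₁n₂/(n₁ + n₂). Stratified: 2 × (100 × 200/300) = 133.3. Unstratified: 300 × 300/600 = 150. The ratio is 0.89, or an effective 267 per group instead of 300.

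**The case against.** The strongest reply is that HPD versus PCOS/POI is not shown to be the study's main contrast. The sample size and the interim rule are built on each group against controls, and the Statistical analysis section speaks only of groups. That stands. The calculation applies only if the two diagnosis groups are compared with each other, which the wording covers but does not single out.

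The harm is also conditional. The 200:100 second stage is stated only for one interim branch. The age range may change but need not, and the same sentence lets group composition change too, which could remove or reverse the imbalance. Adding both age bands might move mean age little. A reader might infer that the groups will differ in age by design; the text supports only that they could.

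A reader might also infer that the plan cannot estimate the biomarkers' diagnostic value. It does not support that either. The regression is to be "to identify the most important associations, appropriate to the endpoint chosen", which leaves room for relevant CAD or plaque as the dependent variable. What is lacking is a commitment to it.

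Finally, covariate lists are often left to a full protocol or analysis plan. That answers a complaint about missing detail. It does not answer this one, because the article itself names unadjusted tests for imaging outcomes and itself makes regression conditional on statistical association.

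**Conclusion.** The concern holds in conditional form. As written, imaging outcomes are compared without adjustment, and regression depends on a screen that neither targets relevant CAD nor secures adjustment for age. On the branch with interim prevalence of at least 10%, if the age range changes and the stated composition is kept, one third of any between-stage difference in prevalence enters the crude HPD versus PCOS/POI contrast.

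The illustrative size is a spurious ratio of 1.14-1.25 or 0.80, with a false-positive rate of 8-27% instead of 5%. These figures rest on assumed prevalence ratios of 1.5-2 or 0.5 and stage-1 prevalences of 6.7% or 13.4%. If the stages have equal prevalence, the bias from this source is zero. The weakness of the significance gate does not depend on the interim decision.

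**What to change.** For any HPD versus PCOS/POI comparison of relevant CAD or plaque, prespecify a logistic regression on diagnosis. Always include age (continuous) and centre, and drop the univariable significance gate. Add recruitment stage where the age ranges overlap enough to separate it from age; with a separate stage-2 age band the two would be strongly collinear. Keep the crude t-tests and chi-square tests as descriptive.

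For the biomarker study, name relevant CAD or plaque as the dependent variable and always include age. No centre term is needed, because the cell-based markers are measured at one centre.

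The change is to analysis wording only: age, centre and stage are known at enrolment. It costs a few degrees of freedom and a small loss of precision. Stratifying by stage alone keeps about 89% of the information under the stated composition.
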